## Abstract

**Background:**

Pregnancy and the postpartum period are times of great change for women and their partners, often bringing substantial challenges and stress. Approximately 10%–20% of women suffer from mood disorders such as depression in the perinatal period. There are risks involved in using psychopharmacological interventions to treat perinatal depression. Mindfulness and compassion-based educational programs could be efficacious and cost-effective options for the prevention and treatment of perinatal mood disorders. The aim of this study is to assess the efficacy of an adapted Mindfulness-Based Childbirth and Parenting (MBCP) program that includes compassion training for pregnant women in primary care (PC) settings in the Spanish National Health System to decrease perinatal depression.

**Methods:**

A multicenter randomized controlled trial (RCT) will be conducted. Participants will be pregnant women (*n* = 122) and their partners who wish to participate. They will be enrolled and assessed in PC settings and randomly assigned to either: (1) an adapted MBCP educational program tailored to the Spanish National Health System + treatment as usual (TAU); or (2) TAU only. The main outcome to be assessed will be depression, evaluated with the Edinburgh Postnatal Depression Scale (EPDS). Secondary outcomes will include self-reported measures of perceived stress, affects, mindfulness, self-compassion, maternal self-efficacy, and use of health and social services. Patients will be assessed at four timepoints: baseline; post-treatment; and at three and six months after childbirth. Intention-to-treat and per-protocol analyses will be carried out using linear regression mixed models. Effect sizes will be estimated using Cohen’s d.

**Discussion:**

Perinatal depression is a significant health problem. An effective and low-cost childbirth education program that incorporates mindfulness and compassion practices may be a beneficial preventive complementary healthcare modality for expectant women and their partners. This study will be the first multicenter RCT in Spanish PC settings using adapted MBCP and compassion practices to reduce symptoms of depression during pregnancy and the postpartum period.

**Trial registration:**

ClinicalTrials.gov, NCT03247491. Registered on 31 July 2017.

## Background

Perinatal depression (PD), which includes major and minor depressive episodes that occur during pregnancy and/or in the first 12 months after delivery, is one of the most common conditions that can develop during pregnancy and the postpartum period [1]. The prevalence of PD in developing countries is approximately 20%; in developed countries, it is in the range of 10%–15% [2]. Untreated PD can have devastating effects on women, infants, and their families [3–5], so much so that NICE guidelines in the UK recommend screening for PD in primary care (PC) settings [6].

Prenatal depression is one of the main risk factors for postpartum depression. It often goes undiagnosed and untreated, with serious consequences for the mother and, by extension, the infant, including growth delays in the developing fetus, prematurity, low birth weight, disorganized infant sleep patterns, and less responsiveness to the external environment [4]. Among Spanish women, the prevalence of prenatal depressive symptoms is approximately 15% [7]. In addition, prenatal depression appears to affect men; thus, the importance of the presence of the partner in interventions tailored to improve couple wellbeing during pregnancy and postpartum is encouraged [8, 9].

Other risk factors for postpartum depression include a young age (e.g. the prevalence of postpartum depression in teenage mothers is much higher than for adult mothers), a previous history of depression, and the presence of postpartum blues: a transient mood disorder characterized by mild depressive symptoms that is common in new mothers [10–13]. A large-scale study conducted in Spain [14] found rates of minor postpartum depression was in the range of 11%–17%, while major postpartum depression was in the range of 8%–11%. Given the prevalence of PD and the adverse effects of this disorder for women, children, and families [3–5], the development and implementation of cost-effective programs and interventions have important health implications. Usual treatments for PD include counseling, psychotherapy, and antidepressant medication. However, there is evidence of risks to both the fetus and breastfeeding infants that limits the use of antidepressants [12, 15], and antidepressant exposure during pregnancy may increase susceptibility to disorders such as hypertension for the expectant woman [16].

Mindfulness-based programs (MBPs) are educational mind–body courses that have the specific purpose of training the mind through meditation practice to adopt a non-judgmental awareness focused on the present moment [17]. In addition, compassion is a particular orientation of the mind that recognizes the universality of suffering in the human experience and cultivates the capacity to meet that suffering with kindness and empathy [18]. It is characterized by the presence of sensitivity to suffering and a commitment to prevent and alleviate it with equanimity and patience [19]. Evidence is growing that compassion is an important mechanism in MBPs and some researchers advocate explicit compassion training within MBPs [20].

MBPs have shown to be beneficial for those with symptoms of depression and other mental disorders [21, 22]. Moreover, some evidence suggests that learning and practicing mindfulness skills during pregnancy may improve both a mother’s symptoms of depression and a baby’s weight at birth [23]. Incorporating mindfulness and compassion into childbirth education could offer pregnant women and their partners at risk for PD, or currently experiencing depression, an alternative strategy for addressing this mood disorder without the stigma that can be associated with psychotherapy or counseling and the risks of antidepressant medication for the mother and the baby [24]. It may also offer a preventive strategy accessible to all pregnant women, as PD can arise without previous risk factors [12].

In addition, mindfulness training has been used as a tool for coping with both chronic and acute pain [25–28]. Thus, a mindfulness and compassion-based program could be useful for expectant women for coping with pain and discomforts often encountered during pregnancy, for childbirth-related pain as well as pain that can arise in the postpartum period, including during breastfeeding. This approach could provide an innovative and complementary skills-based educational approach that promotes physical and mental health and wellbeing during pregnancy, childbirth, and the postpartum period. Such a program could also be beneficial for pregnant women suffering from PD who prefer to avoid medications that may have adverse effects on the fetus and themselves [29], for women who wish to be as thoroughly prepared as possible for whatever may arise during childbirth [30], and for women who have a disposition for making positive behavior changes to improve their physical/mental health during pregnancy [31].

Programs such as Mindful Motherhood [32], Mindfulness-Based Childbirth Education (MBCE) [33], MindBabyBody [34], and the Mindfulness-Based Childbirth and Parenting (MBCP) program [35] have adapted mindfulness training for pregnancy, childbirth, and the postpartum period. MBCP, from which the protocol used in the present study has been specifically adapted, has been shown to decrease fear of childbirth [36] and led to important maternal mental health benefits including improvements in childbirth related appraisals and prevention of postpartum depression symptoms [24]. Other programs, which have been adapted from Mindfulness-Based Cognitive Therapy (MBCT) [37–39], have targeted pregnant women suffering from anxiety and depression and have yielded promising results. In addition, researchers in compassion-focused therapy (CFT) have created compassion interventions for prevention and treatment of PD [40, 41].

The Spanish National Health System (NHS) provides free universal healthcare regardless of financial condition or nationality. However, most regions in Spain do not have specific healthcare professionals who take care of women’s perinatal mental health. With approximately 400,000 births per year in Spain [42], cost-effective and accessible interventions for those coping with PD—as well as a strategy for prevention—are greatly needed. Within this context, the primary aim of the present study will be to compare the effectiveness of an adapted MBCP program with compassion practices that includes treatment as usual (TAU) tailored for delivery in the Spanish NHS and implemented in the second trimester, with an active control group receiving TAU only, to assess possible improvements in depressive symptomatology in pregnant women.

## Methods

### Study design

This is a multicenter randomized controlled trial (RCT) with two parallel groups: (1) adapted MBCP educational course with compassion practices delivered for pregnant women and their partners + TAU; and (2) TAU only, which consists of a childbirth education course provided by PC midwives. This protocol has followed the SPIRIT guidelines [43] Additional file 1. The trial registration number of the study is ClinicalTrials.gov NCT03247491.

### Setting and study sample

Participants will be pregnant women in the second trimester of pregnancy living in the city of Valladolid (Spain) who are served by the Spanish NHS. Partners of the expectant women will be encouraged to participate in the courses. Participants considered for inclusion will be: (1) women in weeks 6–25 of pregnancy; (2) able to read, write, and understand Spanish; (3) age ≥ 18 years ; and (4) have signed a written informed consent document following an informed consent procedure. Exclusion criteria will include: (1) any diagnosis of disease that may affect the central nervous system, such as brain pathology or traumatic brain injury; (2) other psychiatric diagnosis or acute psychiatric illness, such as substance dependence or abuse, a history of schizophrenia or other psychotic or eating disorders; (3) any medical, infectious, or degenerative disease that may affect mood; (4) presence of delusional ideas, hallucinations, or at risk for suicide; and (5) currently under psychopharmacological medication or under psychopharmacological treatment.

### Sample size

The sample size estimation was based on the expectation of a moderate standardized mean difference between groups on depressive symptoms at post-birth of *d* = 0.59. Like the protocol that will be used in the present study, this effect size was found in a recent RCT that used a modified MBCP program [24] compared to a TAU active standard childbirth preparation course with no mind–body components. This effect size is also similar to that obtained in other studies using other programs [44], a pilot study evaluating the effectiveness of MBCE [33], a cohort study assessing the MindBabyBody program [34], and a brief pilot adaptation based upon the MBCP program [9]. Considering a statistical power of 80%, a 5% significance level in a between-group interaction with a local alpha of 0.017 in the first test—using Benjamini–Hochberg’s procedure—and a dropout rate in the range of 15%–20%, as has been observed in these types of studies [45], 61 participants are needed in each group, for a total sample size of 122 women.

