#### Main outcome

The primary outcome will be depressive symptom severity as assessed by the Edinburgh Postnatal Depression Scale (EPDS) [49]. The EPDS is a 10-item self-report scale used to assess the common symptoms of depression (e.g. “I have blamed myself unnecessarily when things went wrong”) during the perinatal period, both pre- and postnatally. It is one of the most widely used instruments to evaluate the severity of PD in clinical trials [50]. Each item of the EPDS is scored on a 4-point scale (from 0 to 3), with the total scale score in the range of 0–30. The validated Spanish version of the EPDS has a cutoff point of ≥ 11 to identify the presence of probable perinatal depression in women, obtaining an area under the curve of 0.98, with also good sensitivity and specificity values [51].

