### Analysis strategy

Results will be reported according to the CONSORT guideline statement [64]. Sociodemographic data at baseline will be presented by means of frequencies (percentages), medians (interquartile range), and means (SD), according to their level of measurement and statistical distribution. Visual inspection on the baseline data will be carried out to check the success of randomization through the two treatment conditions.

The primary efficacy analysis will use an intention-to-treat (ITT) base comparing the main outcome – EPDS – between arms in all the time points as a continuous variable. We will use a repeated measures (RM) design using linear mixed-effects regression models, including participants and the corresponding health center in the random part of the model, by means of the restricted maximum likelihood method (REML). Estimations of slope coefficients (and their 95% confidence intervals [CI]), adjusted for age, nulliparity, previous episodes of depression, and timing of receipt of intervention, will be calculated. To observe the specific trajectories through the study and to evaluate whether possible differences caused by the condition treatment are consistent over time, we will consider the “treatment × time” interaction. In parallel, a per-protocol analysis, with a minimum dose assumed to be ≥ 50% attendance [65], will also be carried out.

If missing data occur in the sample, multiple imputations by using chained equations to replace missing values will be calculated after ensuring data are missing at random (MAR), and as long as there are < 40% missing data in the corresponding variable to ensure validity of imputations [66]. Cohen’s *d* statistic, as an effect size (ES) measure of group differences will be estimated by means of pooled pre-test SDs to weight for the differences in the pre–post means [67]. Values of *d* = 0.20 are regarded as small, 0.50 as medium, and 0.80 large. Secondary analyses will comprise the PSS, PANAS, FFMQ, SCS, and EEP, and will use the same analytical strategy described above.

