Cost-effectiveness and cost-utility procedures of analysis will also be conducted calculating incremental cost-effectiveness (ICER) and incremental cost-utility (ICUR) ratios. The effectiveness of the interventions will be estimated by means of the difference between the EPDS score at baseline and at follow-up; utility will be estimated using quality-adjusted life-year (QALYs) at follow-up. QALYs will be calculated using the area-under-the-curve (AUC). In addition, cost-utility planes will be plotted.

The overall alpha level will be set at 0.05 using two-sided tests and considering Benjamini–Hochberg’s correction for the primary outcome analyses as a way to balance between errors. However, no corrections will be made for secondary outcome analyses.

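### No primary EPDS time point is fixed: sizing uses an undefined post-birth effect, the analysis covers all times, and 61 per arm gives 69–72% power at the stated local alpha of 0.017

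*Protocol article*

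**What the plan says.** All references are to the protocol article.

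- **Main outcome:** "The primary outcome will be depressive symptom severity as assessed by the Edinburgh Postnatal Depression Scale (EPDS"). The section gives no time point.
- **Instruments and Table 1:** EPDS is measured at baseline, after the intervention, and at 3 and 6 months after childbirth. There are thus three post-baseline assessments. The eight pre-birth classes run in the second trimester, so the post-intervention assessment is naturally read as antenatal.
- **Sample size:** the estimate is "based on the expectation of a moderate standardized mean difference between groups on depressive symptoms at post-birth of *d* = 0.59". The calculation then continues: "Considering a statistical power of 80%, a 5% significance level in a between-group interaction", "with a local alpha of 0.017 in the first test" under Benjamini–Hochberg, with 15–20% dropout, giving 61 per arm and 122 in total.
- **Analysis strategy, primary analysis:** an intention-to-treat mixed model "comparing the main outcome – EPDS – between arms in all the time points as a continuous variable". The treatment-by-time interaction is added to judge whether differences are consistent over time.
- **Analysis strategy, error control:** "The overall alpha level will be set at 0.05 using two-sided tests and considering Benjamini–Hochberg’s correction for the primary outcome analyses".

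**The concern.** The sections that bear on the primary endpoint do not point to one result. The outcome definition is silent on time. The sizing effect belongs to a time that is not the name of any scheduled visit and fits two of them. The analysis treats every assessment as primary. The Sample size section calls the powered test an interaction, whereas the Analysis strategy uses the interaction to describe consistency.

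Relief of symptoms in pregnancy, prevention in the early postpartum months and durability to 6 months are different questions. As written, a gain confined to the antenatal assessment could be reported as meeting the primary outcome, although the article ties its expected effect to the period after birth.

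Spreading the primary claim over three tests also lowers the first threshold to 0.017. It therefore matters whether 61 per arm still delivers the stated 80% power at that threshold.

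**Working it through.** **Inputs.** From Sample size: d = 0.59, power 80%, local alpha 0.017, dropout 15–20%, 61 per arm. From Analysis strategy: two-sided tests, overall alpha 0.05. Since 0.05/3 = 0.0167, the local alpha is the first Benjamini–Hochberg step for three tests. That these are the three post-baseline assessments is an inference.

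**Step 1. Reproduce 61 per arm.** Per-arm n = 2(z₁₋α/₂ + z₀.₈₀)² / d².

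- Two-sided 0.017: 2 × (2.387 + 0.842)² / 0.59² = 59.9, so 60 evaluable (62 by the t distribution).
- Inflated for dropout: 60/0.85 = 70.6 and 60/0.80 = 75, so 71–75 randomised per arm (73–78 starting from 62).
- Two-sided 0.05: 46 evaluable (47 by t), so 55–58 randomised (56–59 by t).
- One-sided 0.017: 51 evaluable, so 60–64 randomised. This range contains 61 but conflicts with the stated two-sided tests.

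So 61 fits the two-sided local alpha only if dropout is left out. It does not follow from all the stated inputs together.

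**Step 2. Number analysed.** 61 × 0.80 = 48.8 and 61 × 0.85 = 51.9, so 49–52 per arm.

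**Step 3. Power of a single test.** The noncentrality is d√(n/2): 0.59 × √24.5 = 2.92 for n = 49, and 0.59 × √26 = 3.01 for n = 52. Noncentral t, two-sided:

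| Analysed per arm | alpha 0.05 | alpha 0.017 |
|---|---|---|
| 49 | 0.824 | 0.688 |
| 52 | 0.846 | 0.719 |
| 61 (no dropout) | 0.898 | 0.798 |

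**Step 4. Power under the full step-up procedure.** Benjamini–Hochberg compares the ordered p-values with 0.0167, 0.0333 and 0.05, so 0.017 is not the threshold for every test. Simulation of three equally correlated z-tests (400,000 runs, 49–52 per arm, d = 0.59 wherever an effect exists, assumed correlation 0.3–0.7):

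| True effect at | Power at each such visit | At least one true win |
|---|---|---|
| one visit | about 70–74% | the same |
| two visits | about 76–79% | about 82–90% |
| all three visits | about 80–83% | about 87–95% |

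These use the normal approximation and are slightly optimistic compared with t.

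**Step 5. Error rate.** Three uncorrected independent tests at 0.05 would give 1 − 0.95³ = 14.3%. With Benjamini–Hochberg and no effect at any time, the chance of any false win is about 4.3–5.0% (correlation 0.7 down to 0). With a true effect at one time only, the chance of a false win at either other time is about 4.6–6.0%.

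**Step 6. What could reconcile 61.** Adjustment for a baseline or repeated measure with correlation r multiplies the required n by (1 − r²). Setting 60(1− r²) to 51.85 or 48.8 gives r = 0.37 or 0.43. The article states no correlation.

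**The case against.** **The aim is perinatal.** The Abstract's Background aims at perinatal depression, its Discussion covers both pregnancy and the postpartum period, and the main Background defines perinatal depression as spanning both. An analysis over all times suits that aim, and an antenatal gain is within the stated purpose. This stands. A reader might infer a third conflicting time point from the Background, where the aim is "to assess possible improvements in depressive symptomatology in pregnant women". That phrase names the population enrolled, not an assessment time, so it does not support the inference. The firm mismatch is between Sample size and Analysis strategy, with Main outcome silent.

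**Multiplicity is handled.** A reader might also infer that a win at any visit goes uncontrolled. The article applies Benjamini–Hochberg to the primary outcome, and Step 5 shows that it works close to the 5% level. It controls the false discovery rate rather than strictly the family-wise error, but the excess seen is small.

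**Sized for three tests, not one.** The alpha of 0.017 does allow for three tests; only the effect size belongs to a single, unspecified time. Under the step-up rule, power is near 80% per visit if the benefit is present at all three, and the chance of at least one win is higher still. The 69–72% figure therefore describes the first step and not every scenario.

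**The analysis plan may hold the detail.** A condensed article may leave the list of contrasts to it, and that omission alone would be no finding. But the article itself fixes a sizing target, an alpha split and an all-times primary analysis. These do not identify one endpoint, and the stated sample size does not follow from them.

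**Conclusion.** The point holds in limited form. The article does not fix which EPDS result decides efficacy. Its effect size is for an undefined post-birth time, its primary analysis covers all times, and the three tests implied by 0.017 are not listed. The consequence is not inflated error. It is that an antenatal-only gain could be claimed as the primary success without support from the sizing assumption, and that the stated 80% power is not delivered at the stated alpha.

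The size is 69–72% power at two-sided 0.017 with 49–52 analysed per arm, against 82–85% for one named visit at 0.05. Under the full procedure, power ranges from about 70–74% (benefit at one visit) to about 80–83% per visit (benefit at all three).

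These figures rest on d = 0.59 at each visit with an effect, the stated dropout, a simple two-sample comparison and, for the step-up results, assumed correlations of 0.3–0.7. A baseline correlation of about 0.4 would close the gap, but none is given.

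**What to change.** Before unblinding, name one post-birth visit, for example 3 months after childbirth, as the primary EPDS contrast. Estimate it from the mixed model already planned and test it at two-sided 0.05. Make the antenatal post-treatment EPDS and the other postpartum EPDS key secondary outcomes. State the same visit in Main outcome, Sample size and Analysis strategy. The aim in the Background does not need changing.

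If all three times are to stay primary, list the three contrasts, state which result or combination decides success, and restate the power as about 69–72% at the first step. If a baseline or repeated-measures correlation lies behind 61 per arm, give its value and source.

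The cost is an amendment to the wording and a registry update, with no extra women or data. The downside is that antenatal and other postpartum benefits become secondary claims. Because recruitment has begun, the amendment should be dated and should record that the choice was made blind to results by arm.

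### The stated inputs do not give 61 women per arm: at a two-sided local alpha of 0.017, 61 leaves no room for the 15%–20% dropout it is said to cover

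*Protocol article*

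**What the plan says.** The Sample size section of the protocol article gives every input to the calculation. The effect is a "moderate standardized mean difference between groups on depressive symptoms at post-birth of *d* = 0.59". Power is 80%. The significance level is "a 5% significance level in a between-group interaction with a local alpha of 0.017 in the first test", the first test being that of the Benjamini–Hochberg procedure. Attrition is "a dropout rate in the range of 15%–20%, as has been observed in these types of studies". From these it concludes that "61 participants are needed in each group, for a total sample size of 122 women". Dropout is one of the inputs in that sentence, so 61 is presented as the number to enrol, with losses already allowed for.

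Sidedness is not given there, but the Analysis strategy section supplies it: "The overall alpha level will be set at 0.05 using two-sided tests", with multiplicity handled by "considering Benjamini–Hochberg’s correction for the primary outcome analyses". No within-person correlation, variance reduction or design effect is stated for the sizing.

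**The concern.** A local alpha of 0.017 raises the required number well above that for a single test at 0.05, and dropout raises it again. A figure of 61 per arm looks too small to have absorbed both. If it has not, the stated 80% power does not follow from the stated inputs. A null result on the EPDS would then be read as stronger evidence against an effect of 0.59 than the calculation supports: on the stated basis the type II error is roughly 27–31%, not 20%.

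**Working it through.** **Inputs.** From the Sample size section: d = 0.59 (SD = 1), power 0.80, local alpha 0.017, dropout 15%–20%, 61 per arm. From the Analysis strategy section: two-sided tests.

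**Step 1: reproduce 61.** Analysed women per arm: n = 2(z_alpha + z_power)² / d², with z_power = 0.8416.

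| Alpha | n per arm, normal | n per arm, t | after 15%–20% loss, n/(1 − dropout) |
|---|---|---|---|
| 0.017 two-sided (z = 2.3867) | 59.9, so 60 | 61.3, so 62 | 71–75 (normal), 73–78 (t) |
| 0.05/3 two-sided | 60.2, so 61 | 61.6, so 62 | 72–77 (normal), 73–78 (t) |
| 0.05 two-sided (z = 1.960) | 45.1, so 46 | 46.1, so 47 | 55–58 (normal), 56–59 (t) |
| 0.017 one-sided (z = 2.1201) | 50.4 | 51.5 | 59.3–63.0 (normal, unrounded) |

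First row: 2 × (2.3867 + 0.8416)² / 0.59² = 59.9; 59.9/0.85 = 70.4 and 59.9/0.80 = 74.8. By t, 62/0.85 = 72.9 and 62/0.80 = 77.5.

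The cruder inflation n × (1 + dropout) gives 69–72 (normal) or 72–75 (t) at two-sided 0.017, so it does not reach 61 either.

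Two routes lead to 61. One is two-sided 0.017 (or 0.05/3) with no dropout. The other is one-sided 0.017 with dropout, since 50.4/0.85 = 59.3 and 50.4/0.80 = 63.0. The first leaves out a stated input. The second contradicts the stated two-sided testing.

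**Step 2: women remaining.** 61 × 0.85 = 51.85 and 61 × 0.80 = 48.8 per arm, or about 98–104 in all.

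**Step 3: power at two-sided 0.017.** Power = Φ(d√(n/2) − 2.3867).

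| Analysed per arm | d√(n/2) | Power, normal | Power, t |
|---|---|---|---|
| 61 | 3.258 | 80.8% | 79.8% |
| 51.85 | 3.004 | 73.2% | 71.7% |
| 48.8 | 2.914 | 70.1% | 68.6% |

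The first line confirms that 61 delivers the stated power only if nobody is lost.

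**Step 4: effect detectable with 80% power.** d = (2.3867 + 0.8416)√(2/n). At 51.85 per arm this is 0.634 (t: 0.643). At 48.8 it is 0.654 (t: 0.663). The range is about 0.63–0.66, against the planned 0.59.

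**The case against.** The best reply is that these figures describe a simple two-group comparison of completers at the strictest Benjamini–Hochberg threshold, whereas the plan is richer than that. Three parts of it deserve weight.

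- **Step-up thresholds.** Benjamini–Hochberg relaxes the threshold when other contrasts also succeed. The value 0.017 is about 0.05/3, which suggests three contrasts; that count is an inference. In a simulation with d = 0.59 at all three and correlations of 0.3–0.7 between contrasts (both assumed), power for a given contrast after the stated dropout is about 79–83%. If the effect is present at one time point only, it is about 70–73%.
- **Baseline information.** The primary analysis is a covariate-adjusted mixed model that includes the baseline EPDS. With an assumed baseline to follow-up correlation ρ, the requirement becomes 59.9(1 − ρ²). At ρ = 0.4 that is 50.3, or 59–63 after dropout, which covers 61. At ρ = 0.2 it is 57.5, or 68–72, which does not.
- **Origin of the figure.** It cannot be shown that dropout was forgotten, since a one-sided 0.017 with dropout also gives 61.

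All three stand as limits on what can be claimed. A reader might infer that the whole planned procedure has only about 70% power, or that the authors certainly omitted dropout. The document supports neither. None of this restores the calculation as written, however. It names the 0.017 first test as its basis, gives d as a plain between-group difference and states no correlation. Under two-sided testing, power on that basis is about 69–73% however 61 was obtained.

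**Conclusion.** The point holds as a mismatch between stated inputs and stated result. At d = 0.59, 80% power and two-sided 0.017, 60–62 analysed women per arm are needed and 71–78 must be enrolled to allow for 15%–20% loss; 61 is not that number. On the document's own basis the retained power is about 69–73%, which is 7–11 percentage points below the claim.

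This rests on three readings: the two-sided statement governs the local alpha, lost women contribute nothing to the comparison, and success is judged at the first Benjamini–Hochberg step. It is not an estimate of power for the full mixed-model procedure. That could reach about 80% under favourable assumptions the document does not state. Nor does the point show that more women must be recruited, or that a single contrast should become the sole primary test; the latter would change the planned analysis and is not needed to correct the figure.

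**What to change.** Keep 122 women and rewrite the end of the Sample size paragraph:

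1. State that the local alpha of 0.017 is two-sided, and give the pre-inflation n (60 by the normal approximation, 62 by t).
2. Replace the 80% claim. With 61 randomised per arm and 15%–20% dropout, about 49–52 per arm are analysed. Power for d = 0.59 at two-sided 0.017 is then about 69–73%, and 80% power is reached for d of about 0.63–0.66.
3. If the sponsor holds that 80% is reached through the baseline measurement or the step-up thresholds, state the assumption relied on. Examples are a baseline to follow-up correlation of about 0.4, or an effect of 0.59 at all three post-baseline time points.
4. If a one-sided 0.017 was in fact used for sizing, say so and reconcile it with the two-sided tests in the Analysis strategy section.

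The cost is a few sentences and a less favourable stated power. Recruitment, conduct and the planned analysis are unchanged.
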